#### Blinding

After assigning interventions, participants, investigators, data collectors, outcome assessors, and data analysts will be blinded.

#### Unblinding and emergency unblinding

This study has second-level blinding. After all the research data are checked and locked, the principal investigator (PI) and statistician will conduct the first unblinding, revealing the groups (such as groups A and B) to which each random number belongs. After completing the statistical analysis and clinical trial summary report, the second unblinding will be performed at the closing meeting to uncover the actual drug (QTG or placebo) each group takes.

Emergency unblinding is permissible only in exceptional circumstances, such as severe adverse events suspected to be related to the investigational products when knowledge of the actual treatment is essential for further patient management. Once unblinded, the participant will withdraw from the study. Researchers should report to the PI and ethics committee immediately and report the reasons for unblinding within 24 h. Investigators must record all code breaks with reasons as they occur on the corresponding case report form (CRF) pages.

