#### Criteria for withdrawal, dropout, removal

If the subjects occur severe organ dysfunction, drug allergic reaction, disease deterioration, or serious adverse events during the trial, it is necessary to stop participating in the trial according to the judgment of clinicians; participants can also withdraw from the trial voluntarily due to poor efficacy, intolerance of adverse reactions, and desire to try another treatment methods. Of course, participants may withdraw from the study for any reason at any time. Although the subjects do not explicitly propose to withdraw from the study, they no longer receive medications and examinations and are lost to follow-up. Undoubtedly, this is also withdrawn.

Dropout means that randomized patients prematurely discontinue the study and only complete some of the procedures specified in the trial. For patients who were lost to follow-up or withdraw, efforts should be made by telephone or letter to inquire about the reasons for dropping, investigate their medication history and the time of last taking medicine, and record the outcome measurements at the time of discontinuation. Investigators should try their best to keep subjects enrolled in the study and have the following clinical and laboratory evaluations performed.

Participants may be removed if he/she (1) violates inclusion criteria or meets the exclusion criteria, or receive the wrong treatment assignment; (2) has poor treatment compliance or the number of drugs used does not meet the requirements (<80% or >120%); (3) has incomplete data and no evaluable records after randomization; (4) has used drugs that may influence the efficacy and safety evaluation of the study drug. Removal cases should not be included in the efficacy analysis. However, the safety analysis should incorporate those who receive at least one treatment and have at least one safety record.

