#### Data analysis

The statistical analysis will be conducted using SAS software (version 9.4). According to the “intention to treat” principle, the full analysis set (FAS) is defined as all participants randomized in the trial, with at least one experimental drug treatment history and at least one therapeutic session visit. Per protocol set (PPS), exclude participants found to be ineligible after randomization or deviate from the intervention or follow-up protocols. The safety analysis set will include all randomized patients who have completed at least one study visit. Finally, we will draw conclusions according to the analysis results of FAS. PPS will be used for sensitivity analysis.

For quantitative data meeting normal distribution, means with standard deviations will be calculated, otherwise, medians with quartile ranges will be shown. While for qualitative data, frequencies and percentages will be described. Comparison between groups will be performed by independent t-tests, or Wilcoxon rank-sum test for quantitative data, and the chi-square test or Fisher's exact test for qualitative data. Subgroup analyses will be conducted on those with PHQ-9 or GAD-7 scores ≥ 5 or < 5. Confounding factors that are difficult to control and unbalanced between groups will be used as covariates to analyze covariance to eliminate their influence on efficacy evaluation. *P* < 0.05 will be considered statistically significant. The last observation carried forward is supposed to estimate missing outcome data. Regarding safety, the number of AEs and SAEs will be categorized, and the incidence rate will be calculated. The data monitoring committee is not formally established because the trial has a short duration and known minimal risks. However, some form of data monitoring will undoubtedly be conducted by inspectors appointed by PI to ensure the accuracy and integrity of data.

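### Emergency-unblinded participants must leave the study, not only study drug, which conflicts with the instruction to retain and evaluate participants and puts informative follow-up data at risk

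*Protocol article*

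**What the plan says.** Under Unblinding and emergency unblinding, a code break is allowed only exceptionally, for example for "severe adverse events suspected to be related to the investigational products when knowledge of the actual treatment is essential for further patient management". The consequence is unconditional: "Once unblinded, the participant will withdraw from the study". The reasons must be reported and recorded on the case report form.

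Under Criteria for withdrawal, dropout, removal, the rule after organ dysfunction, allergy, deterioration or a serious event is that "it is necessary to stop participating in the trial according to the judgment of clinicians". People who have ceased both treatment and assessments and cannot be reached count as withdrawn too. For those who withdraw or are lost, staff are to find out why and "record the outcome measurements at the time of discontinuation". The paragraph ends: "Investigators should try their best to keep subjects enrolled in the study and have the following clinical and laboratory evaluations performed".

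The outcome sections and the trial schedule (Table 2) place the exercise test at baseline and week 12 only, and collect composite events and adverse events through week 36. Data analysis fills missing outcomes by last observation carried forward. It also limits the full analysis set to randomized participants with at least one dose and at least one visit during treatment.

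**The concern.** Stopping a drug and leaving a study are different events, and the article uses the language of the second for both. A site that has just broken the code for a suspected drug-related severe event is told in one section that the participant leaves, and in another to retain participants and complete their evaluations. It cannot do both.

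The data at risk come from patients in whom absence is least likely to be random. The reason for unblinding is a suspected effect of the product, so missingness may differ by arm and be related to how the patient is doing. The article claims an intention-to-treat principle and compares the cumulative incidence of composite events at the end of the 24-week follow-up. Both depend on observing patients after they stop treatment, and no analysis can recover data that sites were told not to collect.

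**Working it through.** **The instructions side by side**

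| Situation | Instruction | Drug and follow-up separated? |
|---|---|---|
| Emergency code break | Leaves the study; no exception | No |
| Serious event, allergy, deterioration, organ dysfunction | Stops participation, on clinician judgment | No |
| Withdrawn or lost | Outcomes recorded at discontinuation | Not stated what follows |
| Retention | Keep enrolled and complete later evaluations | Implied, not stated |

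The first and last rows cannot both be followed after a code break. For the second row, the text does not say whether a patient taken off drug is still followed.

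**What is exposed under the unblinding rule as written**

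1. *Primary outcome.* With tests only at baseline and week 12, a patient who leaves earlier and has no test at discontinuation has only the baseline value. Carried forward, change = baseline − baseline = 0 METs, whatever the true course.
2. *Composite and adverse events.* Contacts remaining up to week 36 would not take place. The triggering event is already recorded.
3. *Analysis sets.* The first scheduled visit during treatment is week 4. A patient who leaves before it may fail the full analysis set's visit condition. The safety population is also worded in two ways: "the safety analysis should incorporate those who receive at least one treatment and have at least one safety record" in the withdrawal section and "The safety analysis set will include all randomized patients who have completed at least one study visit" in Data analysis. Whether such a patient counts under the second depends on whether the screening visit qualifies.

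**Is power the problem?** Inputs from Sample size calculation: difference 1.38, SD 1.56, margin 0.42, one-sided 2.5%, power 90%, dropout 20%.

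- Excess over margin: 1.38 − 0.42 = 0.96.
- Normal approximation: n = 2 × (1.960 + 1.282)² × 1.56² / 0.96², which rounds up to 56 per arm. The noncentral t calculation gives 57 (power 0.903).
- Dropout: 57 / 0.8 = 71.25, so 72 per arm and 144 in total. The stated figure reproduces.
- With 150 randomized and 20% lost, 60 per arm remain and power is 0.92 (normal approximation).

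Power is not the issue.

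**Illustration of the bias, on assumed inputs.** If a fraction f of one arm is imputed as zero and their true mean change is x, that arm's mean shifts by f × (0 − x) = −f × x. The article gives neither f nor x. Taking x = −1.56 (one SD of decline):

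| f (assumed) | Shift in arm mean (METs) |
|---|---|
| 1% | +0.016 |
| 2% | +0.031 |
| 5% | +0.078 |
| 10% | +0.156 |

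The standard error of the difference at 75 per arm is 1.56 × √(2/75) = 0.255. At 1–2%, the shift is therefore about 0.06 to 0.12 standard errors. With a decline, it favours whichever arm has more such patients. If their true change were positive, the sign would reverse. Equal fractions and equal true changes in both arms would cancel.

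**The case against.** The best defence is that the withdrawal section already limits the damage. It asks for outcomes at discontinuation, tells investigators to retain and evaluate participants, and keeps treated patients with a safety record in the safety analysis. Stopping after a serious event is left to clinical judgment, and code breaks are exceptional. Some patients could not perform a symptom-limited exercise test after a serious event, so the primary outcome may gain little. A condensed article may also leave off-treatment follow-up procedures to the full protocol.

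Most of this stands, and it rules out several stronger readings that a reader might infer:

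- *That every serious event ends participation.* The text makes this conditional on the clinician. Only the code-break rule is unconditional.
- *That these patients' data are simply lost.* Measurements at discontinuation are requested, and a triggering event that is itself a composite component already counts.
- *That safety follow-up of the event ends at unblinding.* The article does not say so. It requires reporting of serious events and timely treatment of trial-related injury.
- *That the bias can be sized by taking 1.38 METs as the change forgone per patient.* The sample size section defines 1.38 as a between-group difference in improvement, not a change within an arm. Assuming an average benefit also sits badly with the argument that these patients are atypical. No count of affected patients is given.

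The defence does not remove the conflict. The unblinding rule is an explicit statement in the article, not an omitted detail, and it contradicts the retention instruction.

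**Conclusion.** The point holds as a contradiction between two conduct rules, with a limited but informative risk of missing data. The unblinding section requires exit from the study. The withdrawal section wants participants retained and evaluated, and does not separate stopping drug from stopping follow-up when a clinician stops a patient after a serious event. At risk are the week-12 exercise test where none is done at discontinuation, and composite and adverse events to week 36. Zero change carried forward from baseline could hide a deterioration.

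No magnitude is claimed. The group is likely small because code breaks are exceptional, and the illustrative shifts rest entirely on an assumed fraction and an assumed decline. The effect on the primary mean is probably small. The clearer loss is in later event and safety data. This conclusion assumes that sites would read withdrawal from the study as the end of scheduled assessments, which fits how the article uses the word.

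**What to change.** Reconcile the two sections. Leave every decision on study drug and clinical care as it is now, and add a statement on data collection: participants who are unblinded or have stopped treatment remain in follow-up unless they withdraw consent. That covers the week-12 assessment where feasible, the telephone visits, and adverse-event and composite-event collection to week 36. State that they remain in the full analysis set, and use one definition of the safety population in both sections.

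The cost is a short amendment and a note to sites, since the visits and calls are already scheduled. The downside is that some outcomes will be collected after the code is known. Flag these in the database and examine them in a sensitivity analysis.

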#### Sample size calculation

The sample size calculation is based on the superiority trial hypothesis test and is driven by the expected improvement in metabolic equivalents (METs). Referring to data from preliminary clinical trials (27, 28), we assume that the minimum difference in improvements of METs between groups over a 12-week treatment period would be 1.38, and the combined standard deviation would be 1.56. According to relevant literature and experts' advice, the superiority margin is 0.42. Considering a 20% dropout rate and referring to calculation results from PASS 15.0 software, 144 participants would achieve 90% power and a one-sided 2.5% significance level. For the convenience of randomization, a sample size of 150 is identified.

#### Interventions

Concerning standard Western medicine treatment during the trial, according to the guidelines for SCAD treatment (29), antiplatelet drugs, β-blocker, statins, and angiotensin-converting enzyme inhibitors/angiotensin receptor antagonists should be used. Hypoglycemic, hypotensive, and lipid-lowering drugs, as well as other chemical drugs, are permitted depending on the actual condition of the patients. Researchers should record concomitant medications truthfully and maintain dose stability during the trial.

#### Treatment group

The investigational products are produced by the TCM preparation room of Xiyuan Hospital. The composition of QTG includes *Astragali radix* 30 g*, Chuanxiong rhizoma* 10 g*, Paeoniae radix rubra* 10 g*, Corydalis rhizoma* 10 g*,* and *Aurantii fructus* 10 g (Table 1). The pharmacy department purchases and identifies all herbal decoction pieces in QTG. The above five Chinese herbal medicines are prepared in proportion and decocted twice with water, the first time five times water for 30 min, the second time three times water for 20 min, the decoction of two times is combined and filtered, then the filtrate is concentrated into a sugarless paste with a relative density of 1.15–1.25 (50°C). Take the above paste, and add the appropriate amount of dextrin, then QTG is produced using one-step pelletization technology. Granules are packaged into 13 g/bag. Usage and dosage: one bag/time, twice daily, taking medicine orally after mixing it with 150 ml hot water. The treatment course will last 12 weeks. Patients are asked to return unused drugs and drug packages to the investigators at each visit to assess medication adherence.

**Table 1 T1:** The composition of Qixue Tongzhi Granule (intervention drug).

Chinese name	Scientific name	Latin name	Species name	Amount
Huang qi	*Astragalus membranaceus* (Fisch.) Bge.	*Astragali radix*	Leguminosae	30 g
Chuan xiong	*Ligusticum chuanxiong* Hort.	*Chuanxiong rhizoma*	Apiaceae	10 g
Chi shao	*Paeonia lactiflora* Pall.	*Paeoniae radix rubra*	Ranunculaceae	10 g
Yan hu suo	*Corydalis yanhusuo* W.T. Wang.	*Corydalis rhizoma*	Papaveraceae	10 g
Zhi qiao	*Citrus aurantium* L.	*Aurantii fructus*	Rutaceae	10 g

#### Control group

The main ingredients of the placebo granule are caramel and dextrin. In addition, we have added a 10% crude drug of QTG to the placebo granule to achieve smell, color, taste, and texture comparable to that of QTG. Per 13 g/bag of placebo contains 0.0459 g of caramel. The usage and dosage of placebo are the same as QTG.

#### Drugs combined and contraindicated in trial

Patients with sudden onset of angina pectoris can take nitroglycerin or Suxiao Jiuxin Pills under the tongue temporarily. However, they need to detail the date, duration, and alleviation. All newly added medications and treatments other than those originally prescribed drugs should be faithfully recorded in the CRF. During the study period, all other traditional Chinese medicine decoctions, oral or intravenous Chinese patent medicines, or TCM-appropriate technology (including acupuncture or cupping), trimetazidine, coenzyme Q10, and other drugs that may affect the clinical efficacy evaluation are prohibited; anxiolytics or antidepressants are prohibited as well.

#### Follow up

After enrollment, all participants will be followed up four times; the first two times at the 4th and 12th weeks after enrollment are study site follow-ups, while the later two times at the 12th and 24th weeks after treatment are telephone follow-ups.

#### Outcome

The details of items to be measured and time points for data collection are shown in Table 2.

**Table 2 T2:** Trial schedule.

Study phase		Screening period	Intervention period (12 weeks)		Follow-up period (24 weeks)	
Visit		V1	V2	V3	V4	V5
		−3–0 days	Week 4 ± 2 days	Week 12 ± 3 days	Week 24 ± 5 days	Week 36 ± 7 days
Inclusion/exclusion criteria		×				
Informed consent		×				
Random allocation		×				
Baseline data collection	Demographic information	×				
	Medical history	×				
	Past medical history, allergies	×				
Safety evaluation	Vital signs	×	×	×		
	Blood, urine, and stool routines	×	×	×		
	Liver and renal function	×	×	×		
	Blood lipids	×	×	×		
	coagulation function	×	×	×		
	Adverse events		×	×	×	×
Outcome evaluation	CPET	×		×		
	Composite endpoint events		×	×	×	×
	Other indicators in CPET	×		×		
	SAQ, SF-12	×	×	×	×	×
	TCM syndrome scale	×	×	×	×	×
	PHQ-9, GAD-7	×	×	×	×	×
	echocardiography	×		×		
	electrocardiogram	×		×		
	Metabolomics analyses	×		×		
Drug distribution		×	×			
Recovery drug			×	×		
Record drug combination			×	×	×	×
Evaluate compliance				×		

CPET, cardiopulmonary exercise testing; SAQ, seattle angina questionnaire; SF-12, 12 items of short form health survey questionnaire; TCM, traditional Chinese medicine; PHQ-9, patient health questionnaire-9; GAD-7, generalized anxiety disorder-7.

#### The primary and secondary outcomes

The primary outcome is the improvement of METs in CPET. METs are an important indicator for evaluating aerobic metabolism and cardiorespiratory fitness. 1 MET equals 3.5 ml O_2_/kg/min. An increase in exercise capacity manifested by MET can bring great survival benefits. Small increases in cardiorespiratory fitness (e.g., 1–2 METs) are associated with considerably (10% to 30%) lower adverse cardiovascular event rates (30). CPET will be performed at baseline and the end of the 12-week treatment period. Changes from the baseline will be compared between groups.

The secondary outcomes are as follows:
1)Composite endpoint events include cardiovascular death, nonfatal myocardial infarction, revascularization, hospitalization for heart failure or unstable angina pectoris, stroke, and other thromboembolic complications. It will be recorded throughout the study. At the end of the 24-week follow-up period, the cumulative incidence of composite endpoint events will be compared between groups.2)Other indicators in CPET: (a) peak oxygen uptake (PeakVO_2_), percentage of predicted PeakVO_2_, oxygen pulse (VO_2_/Heart rate, VO_2_/HR), oxygen uptake related to work rate (ΔVO_2_/ΔWR), Ventilation Aerobic Threshold (VAT). These indicators reflect exercise capacity and cardiac function. (b) The partial pressure of end-tidal carbon dioxide (PETCO_2_), ventilatory equivalent for carbon dioxide slope (VE/VCO_2_ slope). These parameters measure the body's ability to exchange gases. Comparisons between groups will be made on the 12th week after enrollment.3)Seattle Angina Questionnaire (SAQ). SAQ is a valid self-administered scale that estimates five dimensions of health in patients with SCAD: physical limitation, anginal stability, anginal frequency, treatment satisfaction, and disease perception. SAQ will be measured at every visit. Changes from baseline in each dimension of SAQ will be compared between groups.4)TCM syndrome scale (TCMSS). The TCMSS is composed of related symptoms and signs (chest pain, chest tightness, palpitation, shortness of breath, spontaneous sweating, fatigue, distension in the hypochondrium, abdominal distension, heave a deep sigh, impatience and irritability, tongue manifestation, and pulse condition). Scores are assigned according to the severity of items. Measurement will be performed at each visit. The efficacy evaluation criteria are (a). Markedly effective: Clinical symptoms and signs are significantly improved, and syndrome scores are reduced by ≥ 70%. (b) Effective: Clinical symptoms and signs have improved; syndrome scores have been reduced by ≥ 30% and <70%. (c) Invalid: no significant improvement in clinical symptoms and signs, or even aggravation, syndrome score reduction < 30%. (d) Aggravation: The clinical symptoms and signs were aggravated, and the syndrome score decreased < 0.5)12 items of Short Form Health Survey Questionnaire (SF-12), Patient Health Questionnaire-9 (PHQ-9), and Generalized Anxiety Disorder-7 (GAD-7). SF-12, PHQ-9, and GAD-7 will be measured at each visit to evaluate patients' quality of life and current emotions of anxiety and depression, respectively. Changes from the baseline will be compared between groups.6)ST-T segment change in electrocardiogram, improvement of left ventricular ejection fraction (LVEF), as well as left ventricular end-diastolic diameter (LVEDD) in echocardiography will be compared between groups to assess the effect of QTG on myocardial blood supply and cardiac contractile functions at the 12th weeks after enrollment.7)Metabolomics analyses: Blood samples from ten participants per group will be elected randomly for metabolomic analyses. Liquid chromatography-mass spectrometry (LC-MS) and gas chromatography-mass spectrometry (GC–MS) will be adopted to detect the chemical and biological fingerprints, filter effective components, and explore the underlying metabolic pathways and target molecules of QTG for treating SCAD. Concerning the collection of blood samples, participants should fast for at least 8 h. 5 ml blood will be drawn into heparin sodium anticoagulant tubes, centrifuged, and plasma stored in Eppendorf tubes at −80°C.

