There also exist some limitations to this study. First, a 12-week therapeutic session and a 24-week follow-up visit are set. The relatively short duration of follow-up may be difficult to observe the occurrence of MACEs. However, previous studies have demonstrated that higher exercise tolerance is a good surrogate marker for long-term prognosis (13, 35, 36), so this trial may infer some guidance significance in Chinese herbal medicine improving the prognosis of SCAD. Second, the manufacturers of CPET equipment at four centers are not in full accordance with each other, so this may infer some measurement bias. While we will conduct unified training for outcome assessors concerning the operation scheme of CPET before trial initiation.

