## Conclusion

This randomized, placebo-controlled trial evaluates the efficacy and safety of Qixue Tongzhi Granule in improving the exercise capacity and long-term prognosis of patients with SCAD, which may create a new situation for promoting the application of traditional Chinese medicine in cardiac rehabilitation.

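### Applied as written, the last-observation-carried-forward rule counts patients lost before week 36 as event-free in the composite endpoint; the event-reduction and prognosis wording should match the article's own limitation

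*Protocol article*

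**What the plan says.** Under The primary and secondary outcomes, the composite is the first secondary outcome. It is recorded throughout the study, and when follow-up closes "the cumulative incidence of composite endpoint events will be compared between groups". Table 2 places that last contact at week 36, after 12 weeks of treatment and 24 weeks of follow-up.

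Data analysis gives one missing-data rule: "The last observation carried forward is supposed to estimate missing outcome data". It makes no exception for event outcomes. The only tests named there for categorical outcomes are "the chi-square test or Fisher's exact test for qualitative data". The article names no time-to-event method and no censoring rule.

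On loss, Sample size calculation allows for dropout: "Considering a 20% dropout rate and referring to calculation results from PASS 15.0 software". The withdrawal section lists, as grounds for ending participation on clinicians' judgment, "severe organ dysfunction, drug allergic reaction, disease deterioration, or serious adverse events during the trial, it is necessary to stop participating in the trial". It also asks investigators to record outcomes at discontinuation and to try to obtain later evaluations.

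On claims, the Abstract and Introduction include lower risk of cardiovascular events among the aims. The Conclusion says the trial evaluates the granule in "improving the exercise capacity and long-term prognosis of patients with SCAD". The Discussion concedes: "The relatively short duration of follow-up may be difficult to observe the occurrence of MACEs".

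**The concern.** LOCF was devised for repeated measurements such as a questionnaire score. For an event that accumulates over time, the last observation of a patient lost without an event is simply that no event has happened yet. Carrying it to week 36 turns unknown follow-up into event-free follow-up. Each arm's incidence is then too low, and lower in the arm that loses more patients, so unequal loss can look like a treatment effect. Loss may also be related to outcome, because deterioration and serious adverse events are grounds for leaving the trial.

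Separately, event reduction is listed as an aim and long-term prognosis appears in the Conclusion, while the Discussion admits that events may be hard to observe. A chance result on a handful of events, in either direction, could then be given more weight than it can bear.

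**Working it through.** **1. The plan's own figure.** The sample size concerns metabolic equivalents (METs) only. Inputs from Sample size calculation: difference 1.38, margin 0.42, SD 1.56, one-sided 2.5%, power 90%, dropout 20%.
- Net difference = 1.38 − 0.42 = 0.96.
- Normal approximation: n per arm = 2 × (1.960 + 1.282)² × 1.56² / 0.96² = 55.5, so 56.
- Noncentral t: 57 per arm gives power 0.903 (56 gives 0.898).
- 57 / 0.8 = 71.25, so 72 per arm and 144 in total.

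The stated 144 is reproduced exactly. The article gives no event rate, event count or power for the composite, so every event risk and dropout pattern below is an assumption.

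**2. Effect of carrying event-free status forward.** Let p be the true 36-week risk and d the proportion lost. With a constant hazard λ = −ln(1 − p) over the 36 weeks and loss uniform over that time, a lost patient has an observed event with probability u = 1 − (1 − e^−λ)/λ. The apparent risk is (1 − d)p + d·u. If all loss is at the start, u = 0 and the apparent risk is (1 − d)p.

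For p = 10%: λ = 0.1054 and u = 0.0509.
- d = 10%: 0.9 × 0.10 + 0.1 × 0.0509 = 9.5%.
- d = 20%: 0.8 × 0.10 + 0.2 × 0.0509 = 9.0%.
- d = 30%: 0.7 × 0.10 + 0.3 × 0.0509 = 8.5%.

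| True risk, both arms | 20% lost, uniform | 20% lost, at start | 10% v 30% lost, uniform | Spurious risk ratio, uniform | Spurious risk ratio, at start |
|---|---|---|---|---|---|
| 5% | 4.5% | 4% | 4.8% v 4.3% | 0.90 | 0.78 |
| 10% | 9.0% | 8% | 9.5% v 8.5% | 0.90 | 0.78 |
| 15% | 13.5% | 12% | 14.3% v 12.8% | 0.90 | 0.78 |

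The early-loss ratio is 0.7/0.9 = 0.78. With 20% lost in both arms, each risk is understated by about 10% (uniform) to 20% (at start) in relative terms, and the ratio is nearly preserved.

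**3. Effect on the test.** At p = 10% with uniform loss of 10% v 30%, the gap is 9.51% − 8.53% = 0.98 percentage points, or 0.0098 × 75 = 0.74 of an event in an arm of 75. The exact two-sided Fisher test at 0.05 rejects in 2.9% of trials for 9.5% v 8.5%, against 2.7% for 10% v 10%.

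**4. What the composite can show.** With 75 per arm (150 at 1:1), control risks of 5%, 10% and 15% give 3.75, 7.5 and 11.25 expected control events. Exact Fisher power to detect a halving is 3.7%, 12.8% and 22.9%. By Schoenfeld's formula with two-sided 0.05 and 80% power, a log-rank test needs 4 × (1.960 + 0.842)² / (ln 0.5)² = 65.3, so 66 events, for a hazard ratio of 0.5. A halving at these control risks gives only 75 × 1.5 × (0.05 to 0.15), about 6 to 17 events in total. A time-to-event analysis corrects the handling of loss but not the low power.

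**The case against.** **The method is inferred.** The article does not say that the composite will be compared as crude proportions or that dropouts count as event-free. Cumulative incidence is also the language of Kaplan-Meier and competing-risk estimates, and a statistical analysis plan not shown may specify one. This stands: a missing time-to-event method is not in itself a fault here. But the LOCF sentence is a stated rule without exception, and a censored analysis would contradict it.

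**The 20% is borrowed.** It comes from the sample size for METs. The last two contacts are by telephone, and investigators are asked to pursue patients who leave, so loss for event status may be smaller. Some withdrawals for deterioration may also follow an event that is already recorded. Both points stand.

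**The distortion is small.** It needs unequal or informative loss, and the 10% v 30% split is assumed. In the uniform-loss example the false-positive rate hardly changes. This stands too, and limits the weight of the point.

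**The prognosis claim.** A reader might infer that the composite is being used to support the statement on long-term prognosis. The documents do not support that: the Discussion rests the inference on exercise tolerance as a surrogate, and the Conclusion does not mention the composite. What remains is a mismatch of wording between the aims and Conclusion and the limitation.

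**Event dates.** The article says that events are recorded throughout, not that dates are. Their availability must be confirmed.

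**Conclusion.** The point holds in a limited form. The missing-data rule, applied as written, is unsuitable for an event endpoint: it understates 36-week incidence in both arms and biases the comparison when loss differs between them. If 20% of patients were lost, the understatement would be about 10% to 20% in relative terms. With assumed loss of 10% v 30% and no true effect, the spurious risk ratio is about 0.90 (uniform loss) to 0.78 (loss at the start). With equal loss the ratio is almost unaffected. These figures rest on assumed event risks, a constant hazard and assumed dropout patterns.

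The primary METs analysis is not touched by this point. The composite is an unpowered secondary outcome whose short follow-up the authors disclose, so the correction is worthwhile and cheap but not critical. The aim of reducing event risk and the reference to long-term prognosis are stronger than the stated limitation allows and should be brought into line with it.

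**What to change.** - In Data analysis, exempt the composite endpoint from LOCF.
- Analyse time to first event as adjudicated by the clinical event committee already planned under Quality control. Give Kaplan-Meier or cumulative-incidence estimates by arm, with a simple log-rank comparison or a hazard ratio with 95% CI. Censor at last contact and treat non-cardiovascular death as a competing event. Stratification by centre is optional, given the few events expected.
- First confirm that the case report form captures event dates and the date of last contact.
- Label the result descriptive or supportive.
- Align the event-reduction aim in the Abstract and Introduction, and the prognosis wording in the Conclusion, with the limitation in the Discussion.

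The cost is small: wording, more modest claims and, if dates are not yet captured, an added field on the form. Censoring at last contact still assumes that loss is non-informative, so the numbers lost and the reasons should be reported by arm. The change does not cure the low power.
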